**Study design:**

DUBIUS is a phase 4, multicenter, parallel-group, double randomized study conducted in NSTE-ACS patients designed to compare a pretreatment strategy (including only ticagrelor) versus a downstream strategy (including prasugrel or ticagrelor) and to compare downstream prasugrel with downstream ticagrelor. A total of 2520 patients will be randomly assigned to pretreatment with ticagrelor or to no pretreatment. The PCI group of the downstream arm will be further randomized to receive prasugrel or ticagrelor. The two primary hypotheses are that the downstream strategy is superior to the upstream strategy and that downstream ticagrelor is non-inferior to downstream prasugrel, both measured by the incidence of a composite efficacy and safety endpoint of death from vascular causes, non-fatal MI, or non-fatal stroke, and Bleeding Academic Research Consortium (BARC) type 3, 4, and 5 bleedings.

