### Consenting and randomization

Investigators of each participating site will be cardiologists or cardiology fellows and will assess eligibility, obtain patient informed consent prior to performing any study procedures, enroll eligible patients, and assign patients to interventions. The informed consent form is reported in Additional file 2. All subjects enrolled will be randomly assigned in a parallel 1:1 fashion to downstream administration strategy of P2Y12 receptor blockers (prasugrel or ticagrelor) or to an upstream administration strategy (only ticagrelor) (Fig. 1). The randomization to the upstream or the downstream arm should occur as soon as possible after admission. The patients of the downstream arm, who will undergo PCI, will be further randomized in a 1:1 fashion to downstream prasugrel versus downstream ticagrelor at the time of PCI. The second randomization (prasugrel versus ticagrelor) will occur after coronary angiography and before the PCI procedure. The allocation sequence of patients into study groups will be computer-generated by a central system located at the coordinating center. Allocation sequence will be concealed to investigators. Investigators will obtain the randomization information of patients enrolled at their site by a dedicated online system (https://redcap.dctv.unipd.it). Enrolled subjects and investigators will not be blinded to study treatments, so unblinding will not occur. In order to avoid imbalances between groups with respect to age, all randomizations will be blocked by age > 75 years or ≤ 75 years. On the consent form, participants will be asked if they agree to use of their data should they choose to withdraw from the trial. Participants will also be asked for permission for the research team to share relevant data with people from the Universities taking part in the research or from regulatory authorities, where relevant. This trial does not involve collecting biological specimens for storage. A centralized online system will be used for randomization. Once randomized, the subjects are considered enrolled in the study and analyzed as the intent-to-treat (ITT) population.

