The primary powered hypotheses include (1) superiority of a downstream administration strategy for P2Y12 receptor blockers over the upstream administration and (2) non-inferiority of prasugrel versus ticagrelor in the PCI group of the downstream strategy arm. The study is powered based on the primary endpoint of incidence at 30 days of the combined primary endpoint. For the comparison of upstream and downstream arms, the intent-to-treat (ITT) population will be considered. The study will provide 80% power to establish the superiority of the downstream strategy on the upstream strategy relative to the primary composite endpoint. These calculations are based on the following assumptions: (1) 8% of patients in downstream arm and 11% of patients in the upstream arm (odds ratio = 1.4) having a primary endpoint event within 30 days from randomization, based on extrapolations of previous data. In particular, in patients with NSTE-ACS pretreated with ticagrelor, the 30-day incidence of a composite efficacy endpoint (comprising cardiovascular death, MI, stroke, TIA, or other arterial thrombotic event) was 6.95%, while the rate of major bleeding was 4.05% [19]. In patients with NSTE-ACS not pretreated with a P2Y12 inhibitor, the observed incidence of the composite efficacy endpoint at 30 days (cardiovascular death, MI, stroke) was 7.2%, while the incidence of non-CABG-related TIMI major bleeds was 0.6% and the incidence of all TIMI major bleeds (CABG-related or non-CABG-related) was 1.5% [8]; (2) the time-to-first event analysis based on a 2-sided log-rank test used at a 2-sided significance level (α) of .05 to assess superiority; (3) a dropout rate of about 10%.

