As a second target, non-inferiority of prasugrel versus ticagrelor in the PCI group of the downstream strategy will be considered. Analyses will be performed at the study completion, so no ad interim evaluations are assumed for this study group. Assuming that at least 80% of the patients will have an indication for PCI in the downstream group, based on the above calculations, a sample of about 1000 should be available for randomization in this group. The following assumptions were considered: (i) two-sided non-inferiority test for rejecting the hypothesis that prasugrel and ticagrelor will differ for more than 4% in terms of NACE, (ii) an overall confidence bounds in non-inferiority testing at 0.95 level (α = 0.025), (iii) an overall sample size of 1000 patients (500 prasugrel + 500 ticagrelor), and (iv) an anticipated incidence rate of 5% in downstream ticagrelor and 8.5% in downstream prasugrel and a true difference in incidence rates of 1% between treatment groups [1, 2, 8]. This approach combines the target clinically relevant maximal difference between treatments of 1% with previous information on a relevant distance in terms of effects between treatments (8.5% versus 5%) [21]. This design corresponds to the Palesch and Tilley “futility design” [22, 23], aimed at screening out-of-target therapeutic approaches, in particular in the cardiovascular field [23]. Power calculations have been made using the R-system [24] and gsDesign libraries [25]. For time-to-event variables, survival curves will be constructed using Kaplan-Meier estimates, and log-rank test results will be displayed for descriptive purposes only. Demographics, procedural, imaging, laboratory, exercise testing, quality of life, and diary related data that are not part of the list of endpoints will be displayed for descriptive purposes only.

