**Fig. 2 Fig2:**
[figure not shown]
Study flow chart. *Blood cell count, creatinine, azotemia, pregnancy test (if applicable)

Investigators are requested to adopt strategies to increase the compliance of patients to study protocol and study treatments. At follow-up visits, investigators will actively monitor the adherence to antiplatelet therapy by means of a dedicated questionnaire included in the e-CRF and, when possible, by direct count of drug tablet consumption. For patients not presenting to follow-up visits, investigators will implement strategies of active promotion of the completeness of follow-up including telephone contact, e-mail/letter contact, or any other suitable procedure, as appropriate.

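### Both primary comparisons are planned without baseline covariates, which forgoes a small, low-cost gain in precision; the descriptive-only sentence should exempt pre-randomisation values

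*Protocol article*

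**What the plan says.** All the analysis text is in the Protocol article under Primary and secondary endpoints.

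- Upstream v downstream is powered on "the time-to-first event analysis based on a 2-sided log-rank test" at two-sided 0.05.
- At each of three stages a 95% repeated confidence interval is checked against 0, with critical values from the Farrington and Manning method.
- Prasugrel v ticagrelor is a non-inferiority comparison with a 4-point margin on NACE, 500 patients per group and α = 0.025.
- No covariate is named for any of these.
- The section closes by saying that "Demographics, procedural, imaging, laboratory, exercise testing, quality of life, and diary related data that are not part of the list of endpoints" will be shown for description only.

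The only baseline factor that enters the design is age: "all randomizations will be blocked by age > 75 years or ≤ 75 years". The Fig. 2 footnote shows which blood tests are taken: "Blood cell count, creatinine, azotemia, pregnancy test (if applicable". The figure itself, with the visit schedule, is not shown.

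**The concern.** The primary endpoint combines major bleeding with ischaemic events. Haemoglobin, creatinine, body weight and chronic clopidogrel use can be expected to predict such an endpoint to some degree. Adjusting for them in a randomised comparison lowers the variance of the treatment estimate without extra patients. The plan gives these data a descriptive role only and names unadjusted methods, so that gain is not provided for. It matters somewhat more here because the target difference is 3 points and, on the stated two-sided inputs, power is already below the stated figure. The point concerns prognostic values outside the randomisation factor; the age strata are a separate matter.

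**Working it through.** **1. The plan's own figure.** Inputs: "A total of 2520 patients will be randomly assigned to pretreatment with ticagrelor or to no pretreatment"; "8% of patients in downstream arm and 11% of patients in the upstream arm (odds ratio = 1.4"; two-sided 0.05; 10% dropout; and "The study will provide 80% power to establish the superiority of the downstream strategy on the upstream strategy". A fixed-sample two-proportion calculation, which ignores the staged looks, needs 1499 per arm, or 2998 in all, and 2998/0.9 = 3332 after dropout. The Schoenfeld formula gives 281 events, hence 2958 patients, or 3287 after dropout. Neither gives 2520. Power at 2520 analysed is 72.9%. At 2520 × 0.9 = 2268 (1134 per arm) it is 68.4%, as step 2 shows (68.3% with pooled variance under the null). The gain is therefore measured from 68.4%.

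**2. Superiority, unadjusted.** SE = √[(0.08×0.92 + 0.11×0.89)/1134] = √(0.1715/1134) = 0.01230. Then 0.03/0.01230 = 2.439, and power = Φ(2.439 − 1.960) = Φ(0.479) = 68.4%.

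**3. Superiority, adjusted.** If baseline covariates explain a share R² of outcome variance, the variance of the adjusted risk difference falls by about R², so power = Φ(2.439/√(1−R²) − 1.960). The documents give no R². I take a logistic model with a normal linear predictor and mean risk 9.5%, so R² = var(p)/(0.095×0.905), and read it off for a range of assumed c-statistics. Equivalent extra patients = 2268 × R²/(1−R²).

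| Assumed c | R² | Power | Gain (points) | Equivalent extra analysed patients |
|---|---|---|---|---|
| 0.60 | 1.1% | 68.9% | 0.5 | 26 |
| 0.65 | 2.7% | 69.6% | 1.2 | 63 |
| 0.70 | 5.2% | 70.7% | 2.3 | 125 |
| 0.75 | 8.9% | 72.4% | 4.0 | 222 |

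The gain depends little on the starting point. If power were 80% before adjustment, Φ(2.802/√(1−R²) − 1.960) gives 81.1%, 82.1% and 83.5% at c = 0.65, 0.70 and 0.75.

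**4. Non-inferiority.** The stated rates (5% and 8.5%) do not agree with the stated true difference of 1 point. I use 5% v 6%. SE = √[(0.05×0.95 + 0.06×0.94)/500] = 0.01442. The distance to the margin is 0.04 − 0.01 = 0.03, so power = Φ(0.03/0.01442 − 1.960) = Φ(0.121) = 54.8%. At the lower mean rate of 5.5% the same c-statistics explain less variance:

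| Assumed c | R² | Power | Gain (points) |
|---|---|---|---|
| 0.65 | 1.7% | 55.5% | 0.7 |
| 0.70 | 3.4% | 56.2% | 1.4 |
| 0.75 | 6.0% | 57.4% | 2.6 |

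Other readings of the rates give gains of similar or smaller size. At R² = 5%, power goes from 82.7% to about 84.5% if both rates are 5%, and from 5.0% to 5.1% at 5% v 8.5%.

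**5. Are the data there?** Blood count and creatinine are in the Fig. 2 footnote. Table 1 sets platelet and white-cell limits within 7 days before the index procedure, so a blood count near baseline is needed for eligibility. Table 2 grades bleeding by haemoglobin drop, which requires a reference value. Body weight and chronic clopidogrel use are both needed under Study drugs administration. Haemoglobin is not named as a baseline item, so its availability is inferred.

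**The case against.** The strongest objection is that the sentence is a reporting rule. It lists demographics beside imaging, exercise testing, quality of life and diary data, and most naturally means that non-endpoint variables will not be formally tested as outcomes. A reader might infer that it bars baseline values from the primary models, but the text does not say that. Once that reading is dropped, one may say that only an omission remains, of a kind usually settled in an analysis plan that is not shown.

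The first part stands. The second does not dispose of the point, because the article names specific methods and describes none with a covariate. Under Deviations from the original statistical plan it also treats its own text as the plan, with major changes needing an amendment. An analysis plan that added covariates would sit awkwardly with this wording.

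Three practical objections also have force.

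- Standardising a 30-day risk is not the log-rank test named in the power assumptions, and incomplete follow-up must be handled. The conflict is limited, because the staged interval is checked against 0, the margin is in percentage points, and the same section makes log-rank results for time-to-event variables descriptive.
- The adjusted estimator has to fit the staged looks.
- The trial is open-label and has recruited since December 2015, so a covariate list can only be fixed ahead of comparative analyses still to come.

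A reader might also infer that adjustment is free or would rescue the power. Neither holds: missing covariates could cost patients under the available-data rule unless imputed, and no assumed c-statistic in the range reaches 80%.

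**Conclusion.** The point holds as a minor improvement. The stated primary analyses are valid but unadjusted, and the plan gives non-endpoint demographic and laboratory data only a descriptive role without expressly prohibiting adjustment. The forgone gain is about 1 to 4 points of power for superiority and about 1 to 3 points for non-inferiority, if the baseline values reach a c-statistic of 0.65 to 0.75; at 0.60 it is half a point or less. That range is an assumption, as are the fixed-sample approximation and the 5% v 6% reading of the non-inferiority rates. The mismatch between 2520 and the stated inputs is a larger and separate problem that adjustment does not solve.

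**What to change.** - State that the descriptive-only sentence does not apply to pre-randomisation covariates.
- For both primary comparisons, estimate the marginal 30-day NACE risk difference by covariate standardisation (g-computation). The 4-point margin and the check against 0 stay on the same scale.
- Fix a short list before any further comparative data are analysed: baseline haemoglobin from the blood count, creatinine, body weight and chronic clopidogrel use. Use values recorded before the relevant randomisation: the first for upstream v downstream, the second for prasugrel v ticagrelor.
- Impute missing baseline values simply, so that no patient is dropped.
- Handle incomplete 30-day follow-up, for example by standardising an adjusted time-to-event model.
- Use the adjusted estimate and its standard error in the repeated confidence intervals.
- Report the unadjusted result as support.

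The cost is a documented amendment and modest extra analysis work, with no new patients. If haemoglobin proves not to be recorded at baseline, the list shortens and the gain shrinks.

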### Procedures for accounting for missing, unused, or spurious data

All analyses will be based on available data with missing data excluded. Any unused or spurious data will be noted as appropriate in the final report. Analyses will be compared with a multiple imputation approach to detect potential important influences in the study design due to missing values.

### Deviations from the original statistical plan

Any major changes to the statistical plan described above will be documented in amendment to the clinical investigation plan. Less significant changes to the planned analyses will be documented in the final report.

### Public access policy

The full protocol, the participant-level dataset, and the statistical code may be shared or made public for specific purposes or upon participant’s request with approval of the steering committee. The datasets analyzed during the current study are available from the corresponding author on reasonable request.

### Clinical follow-up and assessment of outcomes

The assessment of clinical endpoints and adverse events will take place during hospital stay, at hospital discharge, at 30 ± 7 days (office visit), and at 12 months ± 30 days (office visit) (Fig. 2). Data collection forms are available in the e-CRF at https://redcap.dctv.unipd.it. e-CRF printout is reported in Additional file 3. Investigators at each eligible site will be preliminarily trained by the coordinating center in order to promote data quality related to both clinical data and clinical events. Clinical documentation of each patient experiencing adverse events will be kept at the enrolling sites and made available for the clinical events committee. Investigators at each site will be trained to collect and report any additional reported adverse events and unintended effects of trial interventions or trial conduct by inclusion in the e-CRF or telephone/e-mail contact with the coordinating center, as appropriate. Outcome data of participants who discontinue or deviate from intervention protocols will be collected in a similar manner to those with a satisfactory adherence to study protocol. The responsible person for pharmacovigilance will be available 24/24 h 7/7 days at [contact] and [contact], [contact], [contact], and [contact]. Data collection forms will be available in the e-CRF at https://redcap.dctv.unipd.it. The e-CRF printout is available in the Trial Master File and in each center in the appropriate section of Investigator’s Site File.

**Fig. 2 Fig2:**
[figure not shown]
Study flow chart. *Blood cell count, creatinine, azotemia, pregnancy test (if applicable)

Investigators are requested to adopt strategies to increase the compliance of patients to study protocol and study treatments. At follow-up visits, investigators will actively monitor the adherence to antiplatelet therapy by means of a dedicated questionnaire included in the e-CRF and, when possible, by direct count of drug tablet consumption. For patients not presenting to follow-up visits, investigators will implement strategies of active promotion of the completeness of follow-up including telephone contact, e-mail/letter contact, or any other suitable procedure, as appropriate.

### Post-trial care

At study completion, each participating subject will receive additional drug treatments or diagnostic investigations according to the treating physician. Subjects who eventually suffered harm from study participation will be cared by the treating physician(s) and may receive compensation upon request to trial sponsor by means of a study-specific insurance policy.

## Study organization

DUBIUS is sponsored by Azienda Ospedaliera di Padova, Padova, Italy. The DUBIUS steering committee is solely responsible for the design and conduct of this study, all study analyses, and the drafting and editing of this and forthcoming manuscripts. Only the steering committee will have full access to the final study dataset, including actual patient data and statistical programming. The steering committee will be responsible for the evaluation of interim analyses and termination of the trial. The steering committee will be responsible for communicating protocol modifications to relevant parties. A clinical endpoints committee will adjudicate primary endpoint events as well as secondary safety events. A statistical analysis center will provide safety data reports and statistical analyses. Safety monitoring will be conducted by a data safety monitoring committee.

Composition, roles, and responsibilities of the steering committee, clinical endpoints committee, and data safety monitoring committee are reported in Appendix 1 (Additional file 4).

### Monitoring

Coordinating investigator (or designees) will monitor the study over its duration according a pre-specified monitoring plan. The study monitor will visit each site at appropriate intervals to review investigational data for accuracy and completeness and ensure compliance with the protocol. The study monitor may inspect all documents and required records that are maintained by the investigator/site, including medical records (office, clinic, or hospital) for the subjects in this study. The investigator/site will permit access to such records. Source documentation must be available to substantiate proper informed consent procedures, adherence to protocol procedures, adequate reporting and follow-up of adverse events, accuracy of data collected on case report forms, and device information. A monitoring visit sign-in log will be maintained at the site. The investigator and/or research coordinator will be available for monitoring visits. It is expected that the investigator will provide the study monitor with a suitable working environment for review of study-related documents. On-site monitoring for the coordinating center will be performed by the sponsor’s Clinical Research Office while remote monitoring for the remaining centers will be performed by the Department of Cardiac, Thoracic, and Vascular Sciences and Public Health of the University of Padova, by means of its Service for Clinical Trials and Biometrics.

According to ICH E6 (R2) GCP, the frequency of monitoring visits is determined by a risk assessment of the trial performed by the sponsor. The first monitoring visit following initiation of the site and trial commencement will take place within approximately 2 weeks after the inclusion of the first patient. Subsequent monitoring visits will take place every 12 months (for the coordinating center) or every 3 months (for the remaining centers). The interval for monitoring visits may be longer or shorter than stated above, depending on subject enrolment rate, quality issues, trial site compliance, or other trial site issues. Any significant deviation from the planned monitoring timelines will be explained and documented in the monitoring visit report and the monitoring plan amended if appropriate. If the site does not enroll any patients or enrolment has stopped, regular monitoring visits will not be scheduled. If there is an extended gap in trial activity, the monitor should ensure that site staff are appropriately trained when trial activities recommence.

### Auditing

Frequency and procedures for auditing trial conduct are described in the monitoring plan. The audit process is independent from both investigators and the sponsor.

### Regulatory agency inspection

In the event that an investigator is contacted by a regulatory agency in relation to this study, the investigator will notify the coordinating investigator (or designees) immediately. The investigator and research coordinator must be available to respond to reasonable requests and inspection queries made during the inspection process. The investigator must provide the sponsor with copies of all correspondence that may affect the review of the current study. The sponsor will provide any needed assistance in response to regulatory inspections.

